# SYNOPSIS

**Study Title**

Etanercept versus Adalimumab in the Treatment of Patients with Ankylosing Spondylitis.

A Switch Study.

**Clinical Phase** 4

**Study Backgrounds**

Ankylosing spondylitis (AS) is a chronic inflammatory arthritis causing back pain, peripheral arthritis and enthesitis. Anti-tumor necrosis factor (TNF) biological agents, including etanercept[1, 2], infliximab[3, 4] and adalimumab[5, 6] had been proved to have dramatic anti-inflammatory and immunomodulatory effect in AS. Infliximab, etanercept and adalimumab are also cost-effective in the treatment of ankylosing spondylitis.[7, 8]

Aanti-TNF therapies have been proved very dramatic efficacy in the treatment of AS, with a 50% reduction of disease activity in about 60% of patients. However, 20% and 30%, are nonresponders or achieve only a partial response. Moreover, in an additional 10-20% of patients, the treatment should be interrupted due to loss of efficacy or side effects over the followup period. In the case of treatment failure with one agent, switching to the other agent may also be useful in patients with AS due to the different chemical structures and mechanisms of action of drugs.

In rheumatoid arthritis (RA), about 20% of patients might not respond to one anti-TNF therapy. Switch studies from one anti-TNF agent to another anti-TNF agent have been done. A systematic review[9] included 33 switch studies in RA showed that most frequently switches are those between etanercept and infliximab. The results are promising but not excellent. Any switch, especially those between monoclonal antibodies, have an effect size that is usually lower than that of a first biologic. When the switch is due to an adverse event with the first TNF-antagonist, however, the response rate of the second one is high. [9]

In a cohort of 282 patients with rheumatoid arthritis treated with infliximab or etanercept, response after switching was recorded as a success for 18 out of the 24 patients who were treated with infliximab first, and for 12 out of the 14 patients who were treated with etanercept first. Among the 29 patients who discontinued the first anti TNF-alpha treatment due to lack of efficiency, only 6 did not respond to the second anti TNF-alpha treatment.[10] A randomised, open-label, clinical trial of 28 RA patients with an inadequate response to etanercept were randomised 1:1 to discontinue etanercept and receive infliximab 3 mg/kg, or to continue etanercept 25 mg twice weekly. At week 16, 62% of infliximab-treated patients achieved American College of Rheumatology 20% criteria for improvement in RA (ACR20) responses compared with 29% of etanercept-treated patients. A 30.8% decrease from baseline in Disease Activity Score 28 was observed in patients receiving infliximab, compared with a 16.0% decrease in patients receiving etanercept. [11]

For spondyloarthropathy (SpA) and psoriatic arthritis (PsA), one report of switching from infliximab to etanercept because of inadequate response or adverse events demonstrated that 9 of 13 patients responded to etanercept and none experienced intolerance to this agent. They suggest that switching between anti-TNF-alpha drugs may be useful for patients with SpA who are unresponsive or intolerant to a first anti-TNF-alpha agent. [12]

For ankylosing spondylitis (AS), a switching study from infliximab to etanercept showed good response for patients who are resistant or intolerant to infliximab. Switching to etanercept after infliximab treatment escape restores the clinical response in the majority of patients. Moreover, etanercept, administered at a dosage of 50 mg once weekly, is effective and well tolerated in patients with AS.[13]. However, no switch study from etanercept to adalimumab was done so far. Thus, we conducted this open label randomized controlled study in etanercept-treated AS patients to analyze the effect of switch to adalimumab.

**Study Objective**

To determine the safety and efficacy of switch effects to adalimumab in etanercept-treated AS patients.

**Study Design**

This single-centre, open-labeled randomized controlled study will evaluate the safetyand efficacy of adalimumab in etanercept-treated AS patients. Thirty patients will be enrolled and randomized equally into two arms. The treatment arm will receive adalimumab 40 mg subcutaneously biweekly for 8 weeks. The control arm will continue etanercept 25 mg subcutaneously twice a week for 8 weeks. At week 8, the control arm will be switched to adalimumab 40 mg subcutaneously biweekly for another 8 weeks. Evaluations will be performed at baseline, weeks 4, 8, 12 and 16**.**

**Patients**

**Inclusion criteria**

1. Diagnosis of AS, as defined by 1984 Modified New York Criteria for Ankylosing Spondylitis
2. Stable background therapy as non-steroid anti-inflammatory for 2 weeks, glucocorticoid for 4 weeks, disease-modifying anti-rheumatic drugs, eg. sulphasalazine, and methotrexate for 8 weeks, anti-TNF biologics for 4 weeks.
3. Written informed consent.

**Exclusion criteria**

1. Serum creatinine  3.0 mg/dl;
2. Alanine aminotransferase (ALT [SGPT])  5 times the laboratory’s upper limit of normal.
3. Pregnant or breast-feeding women.

**Duration of Study:** 16 weeks.

**Number of Subjects** 30

**Number of Study Centers** 1

**Dosage and Administration**

For standard dose（etanercept 50 mg weekly） treated patients, the treatment arm will receive adalimumab 40 mg subcutaneously biweekly for 8 weeks. The control arm will continue etanercept 25 mg subcutaneously twice a week for 8 weeks. At week 8, the control arm will be switched to adalimumab 40 mg subcutaneously biweekly for another 8 weeks.

For half dose （etanercept 25 mg weekly） treated patients, the treatment arm will receive adalimumab 40 mg subcutaneously monthly for 8 weeks. The control arm will continue etanercept 25 mg subcutaneously weekly for 8 weeks. At week 8, the control arm will be switched to adalimumab 40 mg subcutaneously monthly for another 8 weeks.

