**Equivalent dose**

etanercept 50 mg weekly = adalimumab 40 mg biweekly

etanercept 25 mg weekly = adalimumab 40 mg monthly

**Concomitant Treatment** All concomitant treatments (including NSAIDs and corticosteroids) will be recorded on the patient’s case report form including the name of the drug (generic names only except for combination products), total daily dose, and duration of treatment. Additionally, for corticosteroids and NSAIDs, route of administration will be recorded.

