# STUDY FLOWCHART

Abbreviations: BASFI = Bath Ankylosing Spondylitis Functional Index; BASDAI = Bath Ankylosing Spondylitis Disease Activity Index. BAS-G = Bath Ankylosing Spondylitis Global Index.

| **Study Procedures** | **Week**  **-4** | **Week**  **0** | **Week 4** | **Week 8** | **Week 12** | **Week 16** |
| --- | --- | --- | --- | --- | --- | --- |
| Visit ID(for sponsor use only) | 1 | 2 | 3 | 4 | 5 | 5 |
| Signed informed consent | X |  |  |  |  |  |
| Medical history | X |  |  |  |  |  |
| Medical history update |  | X |  |  |  |  |
| Inclusion/exclusion criteria | X | X |  |  |  |  |
| Record prior medications | X |  |  |  |  |  |
| Record concomitant medications |  | X | X | X | X | X |
| Physical examination |  |  |  |  |  |  |
| Vital signs |  | X | X | X | X | X |
| Complete joint assessment |  | X | X | X | X | X |
| Patient global assessment |  | X | X | X | X | X |
| Physician global assessment |  | X | X | X | X | X |
| VAS pain score |  | X | X | X | X | X |
| Nocturnal and total back pain |  | X | X | X | X | X |
| BASFI | X | X | X | X | X | X |
| BASDAI | X | X | X | X | X | X |
| BAS-G | X | X | X | X | X | X |
| Modified Schober’s test |  | X | X | X | X | X |
| Chest expansion measurement |  | X | X | X | X | X |
| Occiput-to-wall distance |  | X | X | X | X | X |
| Serum creatinine | X | X |  |  | X | X |
| ALT (SGPT) | X | X |  |  | X | X |
| Erythrocyte sedimentation rate |  | X |  |  | X | X |
| HS-C-Reactive protein |  | X |  |  | X | X |
| Adverse event evaluation |  | X | X | X | X | X |
| Dispense diary cards |  | X | X | X | X | X |
| Dispense test article |  | X | X | X | X | X |
| BP、BW |  | X | X | X | X | X |
| CBC |  | X | X | X | X | X |
| IgA |  | X | X | X | X | X |
| ASQOL |  | X | X | X | X | X |
| finger to floor test |  | X | X | X | X | X |
| L’t lateral bending |  | X | X | X | X | X |
| Shoulder pain or limitation of motion |  | X | X | X | X | X |
| CONCOMITANT MEDICATION |  | X | X | X | X | X |
| ASAS Criteria for response |  |  | X | X | X | X |
| Patients’ preference scale |  |  | X |  |  | X |

The control group: (n = 15)

Etanercept 50 mg sc. weekly

Ankylosing Spondylitis

The treatment group: (n = 15)

Adalimumab 40 mg sc. biweekly

N=30

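### The protocol describes one regimen per arm in the design and scheme but two, by pre-study etanercept dose, in the dosing text, and randomisation ignores that dose

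*Protocol*

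**What the plan says.** Protocol, Study Design, describes a single regimen for each arm: "The treatment arm will receive adalimumab 40 mg subcutaneously biweekly for 8 weeks" and "The control arm will continue etanercept 25 mg subcutaneously twice a week for 8 weeks", with the controls moving to biweekly adalimumab at week 8. Thirty patients are to be split equally between the arms, and no stratification factor is named.

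The scheme printed below the Study Flowchart also shows one regimen per arm, with 15 patients in each. The control box reads "Etanercept 50 mg sc. weekly" and the treatment box shows biweekly adalimumab.

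Dosage and Administration makes the regimen depend on the etanercept dose before the study. For patients on 50 mg weekly it repeats the design text ("treated patients, the treatment arm will receive adalimumab 40 mg subcutaneously biweekly for 8 weeks"). For patients on 25 mg weekly, "the treatment arm will receive adalimumab 40 mg subcutaneously monthly for 8 weeks" and "The control arm will continue etanercept 25 mg subcutaneously weekly for 8 weeks", and the week-8 switch of these controls is to monthly adalimumab. The Equivalent dose section lists the matching pair: "etanercept 25 mg weekly = adalimumab 40 mg monthly".

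The inclusion criteria require stable anti-TNF treatment for 4 weeks and give no etanercept dose. Statistical Analysis and Rationale for Number of Subjects do not mention dose group; the latter uses one pair of expected BASDAI changes and one SD.

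**The concern.** Both descriptions cannot hold for a patient who enters on etanercept 25 mg weekly. Staff at the single centre working from Study Design or the scheme would give such a patient a different regimen from staff working from Dosage and Administration. This applies in either arm, and again after week 8. A statistical analysis plan would not normally settle which treatment a patient is assigned.

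The same gap leaves the estimated contrast unclear. It may be one comparison (biweekly adalimumab against etanercept 50 mg weekly), or a mixture of that and a second comparison at half the adalimumab frequency and half the weekly etanercept, in proportions the protocol does not fix. If the mixture is intended, pre-study dose is a known two-level factor that decides what each arm receives, yet the allocation does not use it. With 30 patients the two arms could end up with noticeably different mixes.

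**Working it through.** **1. The sections side by side, for each pre-study etanercept dose**

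| Section | 50 mg weekly before study | 25 mg weekly before study |
|---|---|---|
| Study Design | Adalimumab 40 mg biweekly v etanercept 25 mg twice a week; switch to biweekly | Not mentioned; the one stated regimen covers all 30 |
| Dosage and Administration | Same as Study Design | Adalimumab 40 mg monthly v etanercept 25 mg weekly; switch to monthly |
| Equivalent dose | Pair listed | Pair listed |
| Scheme under Study Flowchart | 15 on adalimumab 40 mg biweekly, 15 on etanercept 50 mg weekly | Not mentioned; 15 + 15 = 30 already uses every patient |
| Inclusion criteria | No dose stated | No dose stated |

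The right-hand column is the conflict. In the left-hand column the sections agree on weekly dose: 2 × 25 mg = 50 mg, and Dosage and Administration itself uses the two forms for the same patients.

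**2. Chance imbalance under an unstratified 15:15 split**

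The protocol gives no figure on this point and does not state the number K of half-dose patients, so I assume K = 6, 10 and 12 of 30. The number X who fall in the adalimumab arm is hypergeometric (30 patients, K half-dose, 15 drawn). The arms differ by |2X − K|.

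- K = 6: a difference of 4 or more means X ≤ 1 or X ≥ 5. Probability 2 × (0.0084 + 0.0759) = 0.169.
- K = 10: X ≤ 3 or X ≥ 7. Probability 2 × (0.0001 + 0.0025 + 0.0225 + 0.0975) = 0.245.
- K = 12: X ≤ 4 or X ≥ 8. Probability 0.264.

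**3. What one such split would do to the estimate**

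Inputs: 15 per arm and SD 2 (protocol); target difference (4 − 2) − (4 − 3.5) = 1.5 points (Rationale for Number of Subjects); a 1-point difference in mean BASDAI between dose groups (assumption).

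- Shift from a 7:3 split: (7 − 3)/15 × 1 = 0.27 points.
- Standard error of the difference: 2 × √(2/15) = 0.73 points.
- Shift in standard errors: 0.27/0.73 = 0.37.
- Shift against the target difference: 0.27/1.5 = 18%.

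**4. How much variance the stratum could explain**

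With a 1-point gap and half-dose share p = K/30, the variance between dose groups is p(1 − p). Divided by the total variance SD² = 4, this is 0.16/4 = 4% for K = 6, 0.222/4 = 5.6% for K = 10 and 0.24/4 = 6% for K = 12. The gain in precision from adjustment would be modest.

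**The case against.** The strongest reply is that Study Design is an overview and Dosage and Administration the operative text. The latter is explicit for both arms and for the week-8 switch and is backed by the equivalence list, so a half-dose patient does have instructions. The scheme survives only as fragments of a diagram. This makes the conflict easier to repair, but does not remove it. The design text and the scheme are not worded as covering only some patients, the scheme's 15 + 15 uses up the whole sample, and eligibility is silent on dose.

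Three stronger readings are tempting, and the documents do not support them.

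- A reader might infer that imbalance in dose group biases the comparison. It does not. Each dose group has its own matched pair of regimens, and 1:1 randomisation is unbiased over allocations, so a 7:3 split is random error of the kind the test and interval already allow for. A stable difference in level would also largely cancel in change from baseline.
- A reader might infer that the control regimen is contradictory because 25 mg twice a week stands in one place and 50 mg weekly in another. The weekly total is the same, so at most the injection schedule is abbreviated.
- A reader might infer that the analysis is wrong because it has no dose term. Covariates and subgroup displays are commonly left to a statistical analysis plan, which is not at hand, so their absence here is not an error.

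It can also be said that stratification is optional in a trial of 30. That is fair as a general rule. The case here is that the factor is binary, known before randomisation, and decides the regimen itself.

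**Conclusion.** The point holds as an internal inconsistency in the protocol about the population and the regimens, together with an allocation that ignores the dose on which the regimen depends. The inconsistency is textual and needs no assumption.

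The statistical consequence is limited. The figures of 17%, 25% and 26%, and the 0.27-point shift, rest on an assumed number of half-dose patients and an assumed 1-point gap, neither of which the documents give. Even granting both, the shift is about a third of a standard error and the stratum explains about 4% to 6% of the variance. The main gain is a defined treatment contrast; protection against chance imbalance is a smaller one. The change should be made, but it does not put the validity of the randomised comparison in doubt.

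**What to change.** Reconcile Study Design, Inclusion criteria, Dosage and Administration, Equivalent dose and the scheme under the Study Flowchart, so that one description of the population and of the regimens in each arm, before and after week 8, holds throughout. Which description is right is for the sponsor to decide.

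If both dose groups stay:

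- stratify the 1:1 randomisation by pre-study etanercept dose (50 v 25 mg weekly);
- include that stratum in the between-arm week-8 analysis, whichever method is chosen (the only test the protocol names is the paired t test);
- show results by dose group descriptively. With 10 half-dose patients, for example, there would be about 5 per arm, too few for a separate test.

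If only one group stays, the inclusion criteria should state the pre-study dose and the text for the other group should go.

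Cost: protocol wording, two randomisation lists instead of one, and one model term. No extra patients are needed. With two lists the final arm sizes may depart slightly from 15:15. As the trial is open-label, block sizes should not make the next allocation predictable.

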**Equivalent dose**

etanercept 50 mg weekly = adalimumab 40 mg biweekly

etanercept 25 mg weekly = adalimumab 40 mg monthly

**Concomitant Treatment** All concomitant treatments (including NSAIDs and corticosteroids) will be recorded on the patient’s case report form including the name of the drug (generic names only except for combination products), total daily dose, and duration of treatment. Additionally, for corticosteroids and NSAIDs, route of administration will be recorded.

**Prohibited:**

1. Any new treatment with a DMARD or a cytotoxic (immunosuppressive) drug except for hydroxychloroquine, sulphasalazine, and methotrexate
2. Surgical joint interventions (open or arthroscopic) .

**Efficacy Evaluation**

**Primary Efficacy Endpoint:**

- The primary endpoint of this study is Bath AS disease activity index (BASDAI) at week 8.

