**Secondary Efficacy Endpoints will include:**

- ASAS20 response rate
- Mean change in each of the following domains:
  - VAS patient global assessment
  - VAS pain score
  - Bath AS functional index, BASFI
  - Bath AS global index, BAS-G
  - BASDAI –two morning stiffness-related scores
- Patient global assessment, physician global assessment, nocturnal and total back pain, the BASFI and its independent components, and the BASDAI and its independent components.
- Spinal mobility measured with modified Schober’s test, chest expansion, and occiput-to-wall measurement.
- Patients’ preference scale.
- Quality of life as ASQoL questionnaire.
- Laboratory assessment of inflammation with HS-CRP, Immunoglobulin A and ESR
- Serum creatinine、ALT (SGPT)、CBC

**Safety Evaluation** All patients who receive at least 1 dose of test medicine will be evaluated for safety. The following variables will be assessed: physical examination/vital signs, haematology and chemistry profiles, urinalysis, assessment of extra-spinal and extra-articular involvement, premature withdrawal, adverse events, and serious adverse events during the study.

**Statistical Analysis** Descriptive statistics such as number of observations, mean, median, standard deviation, minimum, maximum and 95% confidence interval will be used to summarize the continuous variables. Frequency and proportion will be used to summarize the categorical variables. The primary analysis will be performed based on the intent-to-treat population. All statistical tests will be two-sided which was evaluated at 5% level significance.

Frequency of dropouts, premature termination of study medication, and withdrawal will be provided and summarized. The last-observation-carried-forward (LOCF) approach will be used to evaluate missing data.

Summary tables for demographic data and baseline characteristics will be provided.

The primary efficacy endpoint is the number of responders as determined by the ASAS Response Criteria for improvement at 20% level at week 8. All patients who withdraw before 8 weeks will be considered non-responders for this endpoint.

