Changes (and percentage changes) from baseline at each visit in the individual components of the ASAS Working Group criteria (VAS patient global assessment, VAS physician global assessment, VAS total and nocturnal pain, BASFI, BASDAI and BAS-G), spinal mobility measures, complete joint assessment, evaluation of hip involvement, and laboratory assessments of inflammation will be analyzed by using paired-t test.

The number and percentage of patients who experience adverse events will be summarized. The number and percentage of patients who experience potentially clinically significant changes in laboratory results, and those who discontinue, will be tabulated. Transition tables from baseline for physical examination and laboratory results will be summarized.

**Rationale for Number of Subjects** Assuming that the BASDAI scores of treatment group (μ1) reduced to 2 from 4, and the BASDAI scores of control group (μ0) reduce to 3.5 from 4. A 2-side test was used, with type Ⅰ error () = 0.05, statistical power (1-) = 0.8 and standard deviation (SD) = 2. The expected dropout rate is 10% in this research. Finally, the study required only 14 subjects in each group to achieve 95% power. The targeted sample size for the study was 30 patients. Therefore, the study had  95% power to detect a treatment effect with this sample size.

**Ethical Considerations** This study will be conducted in accordance with applicable laws and regulations including, but not limited to, the International Conference on Harmonization Guideline for Good Clinical Practice (GCP) and the ethical principles that have their origins in the Declaration of Helsinki. The institutional review board (IRB)/independent ethics committee (IEC) must review and approve the protocol and informed consent form (ICF) before any subjects are enrolled. The subject must be consented using the approved ICF before any procedures specified in the protocol are performed.

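### The BASDAI primary endpoint is a week-8 score, but the only analysis stated for BASDAI is a paired t test on change; a between-arm, baseline-adjusted comparison should be named and the SD of 2 identified

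*Protocol*

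**What the plan says.** Three places in the Protocol synopsis bear on the form of the BASDAI endpoint.

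- **Primary Efficacy Endpoint:** "The primary endpoint of this study is Bath AS disease activity index (BASDAI) at week 8". This is a level, with no mention of change.
- **Statistical Analysis:** "Changes (and percentage changes) from baseline at each visit in the individual components of the ASAS Working Group criteria", a list that includes BASDAI, with the closing words "laboratory assessments of inflammation will be analyzed by using paired-t test". This is the only test named for BASDAI. The sentence does not call it the primary analysis.
- **Rationale for Number of Subjects:** BASDAI is assumed "reduced to 2 from 4" in the treatment group and to "reduce to 3.5 from 4" in the control group, with "standard deviation (SD) = 2". The text does not say which quantity has that SD.

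The Study Flowchart schedules BASDAI at week 0 and week 8, so a baseline value is already collected. Separately, Statistical Analysis names a different primary: "The primary efficacy endpoint is the number of responders as determined by the ASAS Response Criteria for improvement at 20% level at week 8". That conflict has to be settled first. The present point is what remains if BASDAI is kept.

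**The concern.** A paired t test looks at change within patients. It does not compare adalimumab with continued etanercept, which is what the randomisation is for. Without a stated between-arm analysis, a reader has to supply one, and the text offers three candidate variables: week-8 level, change and percentage change.

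These have different variances. They also give different estimates from the same data whenever the arms' baseline means differ by chance, as they will with 15 per arm. The level carries into week 8 whatever part of that imbalance persists. The change subtracts all of it, which is too much unless baseline predicts week 8 point for point.

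What is at stake is precision, and a choice of form that should be closed before the data of an open-label trial are seen.

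**Working it through.** **Inputs from the Protocol.** 15 per arm; two-sided 5%; BASDAI 4 to 2 and 4 to 3.5; SD 2. Both arms start at 4, so the planned difference is 3.5 − 2 = 1.5 on the level and 2 − 0.5 = 1.5 on the change. Only the SD is ambiguous.

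**Assumption not in the Protocol.** The baseline to week-8 correlation ρ, taken as 0.3 / 0.5 / 0.7.

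**1. The plan's own figure.** The Rationale claims 14 per group for 95% power. The two-sample formula n = 2(z₀.₉₇₅ + z_power)² SD² / Δ² gives:
- 95% power: 2 × (1.960 + 1.645)² × 4 / 2.25 = 46.2, so 47 per arm.
- 80% power: 2 × (1.960 + 0.842)² × 4 / 2.25 = 27.9, so 28 per arm.

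The stated figure is not reproduced. Power by the noncentral t is 48% at 14 per arm and 51% at 15. Of the formulas tried, only a one-sample calculation comes near (fall of 2, SD 2, 95% power: n = 13), and that is not a comparison between arms.

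**2. SD of the change if 2 is the SD of the score.** SD_change = 2√(2(1 − ρ)) = 2.37 / 2.00 / 1.55. Score and change have the same SD only at ρ = 0.5.

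**3. Chance baseline imbalance.** SD of the difference in baseline means = 2√(2/15) = 0.73, about half the 1.5 target. It exceeds 1.0 in either direction in 17% of trials.

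**4. Simulation.** Bivariate normal baseline and week-8 scores, SD 2 at both visits, 15 per arm, 100,000 trials per setting. Two-sample t tests on level and on change, and ANCOVA of week-8 score on arm and baseline. The two-sample test on change is supplied here; the Protocol does not state it.

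| | ρ = 0 | ρ = 0.3 | ρ = 0.5 | ρ = 0.7 |
|---|---|---|---|---|
| Power, level | 51% | 51% | 51% | 51% |
| Power, change | 29% | 39% | 51% | 73% |
| Power, ANCOVA | 49% | 53% | 61% | 78% |
| Level and change disagree at p<0.05, planned effect | 31% | 32% | 34% | 40% |
| Level and change disagree, no effect | 7% | 8% | 8% | 9% |
| Type I error if either may be reported | 9% | 9% | 9% | 9–10% |

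Each test on its own holds 5% type I error.

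**5. If 2 is instead the SD of the change.** The SD of the score is 2 / √(2(1 − ρ)) = 1.69 / 2.00 / 2.58 at ρ = 0.3 / 0.5 / 0.7. Power is then about 51% on the change and 65% / 51% / 33% on the level; disagreement is 32% / 34% / 39%.

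**6. How much of the disagreement is low power.** With 47 per arm and the inputs of step 4, disagreement falls to about 13% / 8% / 5% at ρ = 0.3 / 0.5 / 0.7.

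**7. Why ANCOVA removes the choice.** If week-8 score = a + τ·arm + β·baseline + error, then change = a + τ·arm + (β − 1)·baseline + error. The arm coefficient τ, its standard error and its p-value are identical.

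**The case against.** A reader might infer that the Protocol defines its primary in two contradictory ways, as a level and as a change. The text does not support that. Only the endpoint section names BASDAI as primary, and it gives one form. The change sentence is a general list covering many measures at every visit, and it can be read as supporting analysis. On that reading there is no contradiction, but the named primary is left without a stated between-arm analysis, so the point survives in this form.

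A reader might also infer that a third of trials would reverse their conclusion because of this wording. That figure depends on an assumed correlation, on the full 1.5-point effect, and on a between-arm test of change that the Protocol does not name. It also falls sharply at an adequate sample size. The sample-size shortfall drives it more than the wording does.

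Two more objections stand. Under randomisation neither level nor change is biased, and the 9% error rate arises only if someone reports whichever test is significant, which no passage permits. And covariate adjustment is commonly left to a statistical analysis plan, so its absence alone is no fault. The case for ANCOVA here is that the one test the Protocol does name for BASDAI does not compare the arms and has to be replaced or supplemented anyway.

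**Conclusion.** The point holds as a gap in the analysis and a cheap improvement, not as a direct contradiction. The primary is worded as week-8 BASDAI, the only stated BASDAI analysis is a within-patient test on change, and the SD of 2 is unidentified.

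Under the planned effect, with SD 2 at both visits and an assumed correlation of 0.3 to 0.7, baseline-adjusted ANCOVA has 53% to 78% power, against 51% for the level and 39% to 73% for the change. Near zero correlation it gains nothing over the level (49% against 51%). It does not rescue the sample size: none of these reaches the 80% that the Rationale takes as its input, or the 95% that it claims.

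**What to change.** Settle first whether BASDAI or ASAS20 is primary. If BASDAI is kept:

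- In both Primary Efficacy Endpoint and Statistical Analysis, write: *BASDAI at week 8, compared between randomised arms by ANCOVA with week-0 BASDAI as covariate.*
- Report the adjusted mean difference with its 95% confidence interval.
- Keep raw and percentage changes, and any paired tests on them, as descriptive within-arm summaries.
- In Rationale for Number of Subjects, have the sponsor state whether the SD of 2 is that of the score or of the change. The document does not settle this, so it should not be assumed either way. The calculation should then be redone for the between-arm comparison.

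The cost is wording and one degree of freedom for the covariate. No new visits, measurements or patients are needed for the change of analysis.

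### Two different week-8 variables, BASDAI and the ASAS20 responder count, are each named as the primary endpoint

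*Protocol*

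**What the plan says.** Under Efficacy Evaluation, the protocol states: "The primary endpoint of this study is Bath AS disease activity index (BASDAI) at week 8". The secondary list that follows opens with "ASAS20 response rate" and also includes BASDAI and its components, with no time point.

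The Statistical Analysis section then states: "The primary efficacy endpoint is the number of responders as determined by the ASAS Response Criteria for improvement at 20% level at week 8". It adds a rule for that variable: "All patients who withdraw before 8 weeks will be considered non-responders for this endpoint". The general rule, a few lines earlier, is "The last-observation-carried-forward (LOCF) approach will be used to evaluate missing data". The significance level is set once for everything: "All statistical tests will be two-sided which was evaluated at 5% level significance".

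The Rationale for Number of Subjects uses BASDAI means only. It begins "Assuming that the BASDAI scores of treatment group (μ1) reduced to 2 from 4" and gives no ASAS20 response rate. The document contains no co-primary wording, no testing order and no division of the 5%.

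**The concern.** A protocol must name the result on which the trial will be judged. A statistical analysis plan can elaborate that choice, but here its author could cite either sentence as authority, so the conflict cannot be left to that document.

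The choice matters for three reasons.

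- **Analysis.** BASDAI is a score and the ASAS20 count is binary, so the tests differ, and so does the treatment of patients who withdraw before week 8.
- **Sizing.** If the Statistical Analysis sentence governs, the primary endpoint has no sample-size basis at all.
- **Selection.** The trial is open-label, and week 8 is the last visit before the control arm also switches to adalimumab. With two texts to point to, the primary result of that randomised comparison could be picked once the data are known.

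**Working it through.** **Inputs**

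- Level: two-sided 5% for all tests (Statistical Analysis).
- Size: 30 patients randomised equally, so 15 per arm (Study Design; Study Flowchart).
- Expected dropout: 10% (Rationale for Number of Subjects).
- Correlation between the two test statistics: not given; assumed from 0 to 0.9.
- Test for ASAS20: not named; two cases are shown below.

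**1. The statements side by side**

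| Place in the protocol | BASDAI, week 8 | ASAS20, week 8 |
|---|---|---|
| Primary Efficacy Endpoint | primary | not named |
| Secondary Efficacy Endpoints | listed, no time point | listed, no time point |
| Statistical Analysis, naming of the primary | not named | primary |
| Withdrawal before week 8 | LOCF (general rule) | non-responder |
| Named test | paired t-test on changes | none |
| Sample-size assumptions | yes | none |

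The paired t-test entry comes from the sentence that ends "laboratory assessments of inflammation will be analyzed by using paired-t test"; its list of variables includes BASDAI.

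**2. What the sample size covers**

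The assumed week-8 means are 2 and 3.5, a difference of 1.5, with SD 2. At the stated 14 per arm, by the normal approximation:

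power = Φ(1.5 / (2 × √(2/14)) − 1.96) = Φ(1.984 − 1.960) = Φ(0.024) ≈ 0.51

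This does not reproduce the stated 95%. That is a separate problem and the present point does not depend on it. What matters here is that every input is a BASDAI quantity.

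**3. Patients affected by the missing-data rule**

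15 × 0.10 = 1.5, so one or two patients per arm would be handled differently according to which variable is primary.

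**4. Type I error if success on either endpoint were accepted, both tests using their full 5%**

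- Independent: 1 − 0.95² = 0.0975.
- Correlated, bivariate normal: 1 − P(|Z₁| < 1.96 and |Z₂| < 1.96).

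| Assumed correlation | Type I error |
|---|---|
| 0 | 0.0975 |
| 0.3 | 0.0951 |
| 0.5 | 0.0907 |
| 0.7 | 0.0835 |
| 0.9 | 0.0704 |

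**5. The same, with ASAS20 tested by Fisher's exact test**

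At 15 per arm this test is conservative. Its true size is the total probability, under a common response rate, of all tables with p ≤ 0.05. For common rates of 0.2, 0.3, 0.4 and 0.5 it is about 1.6% to 1.7%. Whatever the correlation, the combined error cannot exceed the sum of the two sizes:

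0.05 + 0.017 = 0.067

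**The case against.** The strongest reply is that the intent is clear. The dedicated endpoint section, the listing of ASAS20 as secondary and the sample-size rationale all point to BASDAI, and one sentence departs from them. This stands as evidence of intent, and the fix relies on it. It does not remove the conflict, because that sentence is the only one in the Statistical Analysis section that names a primary endpoint.

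A reader might draw four stronger conclusions that the document does not support.

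- **That the trial runs at nearly 10% type I error.** Nowhere does the protocol say that success on either endpoint counts. The sentence on the 5% level sets a threshold for each test and does not make the two variables alternative primaries; an ordinary secondary endpoint would be tested at the same level. The upper figure also needs independence and an ASAS20 test that uses its full 5%.
- **That the two missing-data rules are themselves an error.** Counting withdrawals as non-responders for a binary variable is compatible with LOCF elsewhere. The difference matters only because the primary is undecided.
- **That ASAS20 power can be worked out from the Study Backgrounds.** The 62% and 29% quoted there are ACR20 rates from a rheumatoid arthritis trial in inadequate responders to etanercept. This trial's inclusion criteria do not require inadequate response, so those rates say nothing about ASAS20 power here.
- **That BASDAI should leave the secondary list altogether.** It is scheduled and analysed at other visits too. Only its week-8 total duplicates the primary.

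**Conclusion.** The contradiction is explicit in the current text and must be resolved before analysis. What is shown is an ambiguous designation that leaves room to choose the primary result after the data are seen.

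Inflated type I error is a possible consequence, conditional on an either-endpoint success rule that the protocol does not state. Under that rule the error would be about 7% to 9.8% if both tests use their full 5% (assumed correlation 0.9 to 0). It would be at most about 6.7% with Fisher's exact test for ASAS20 at 15 per arm, taking its true size as 1.7%.

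**What to change.** - **Primary endpoint.** Keep BASDAI at week 8 as the sole primary endpoint, as the Primary Efficacy Endpoint section and the sample-size rationale support.
- **Statistical Analysis.** Replace the sentence that calls the ASAS20 count primary with wording such as: *The proportion of ASAS20 responders at week 8 is a secondary endpoint; a patient who withdraws before week 8 counts as a non-responder.* Add: *Only BASDAI at week 8 is tested confirmatorily, at the two-sided 5% level.*
- **Secondary list.** Limit total BASDAI to visits other than week 8 and keep its components.

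The cost is protocol wording only, with no change to visits or data. ASAS20 gives up any claim to confirmatory status.
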